### Sample size

The sample size is calculated with reference to relevant previous studies. Notably, a change in VAS of knee pain is estimated to be 2.0 between two groups after the strengthening program, which suggests clinically important change. Meanwhile, the standard deviation (SD) between the experiment and the control groups is estimated to be 2.5 based on relevant previous publications [20]. Moreover, the sample size required for each group is about 33 when a two-tailed test with the power of 90% and the significance level of 5% (α error) is applied. Eventually, the total sample size is calculated to be 80 after taking into consideration a 1:1 allocation ratio and a dropout rate of 20%.

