Patients will be required to carry out each exercise for 10 repeats at home as a set, for 3 sets each time and twice a day for 6 weeks altogether. Qualified physiotherapists who have attained the physical therapist’s certification with over 5 years of experience will be trained beforehand, so as to instruct and guide patients in carrying out these exercises. All exercises are standardized; however, the resistance for each movement should be decided according to the practical situation of each patient. As a result, all participants will have to visit the physiotherapists in the Affiliated Hospital of Southwest Medical University once a week for 6 weeks, so as to learn the exercises and adjust the training intensity. Typically, progression to a greater resistance level is possible when participants can perform 20 repeats of a given exercise without fatigue. Moreover, graded resistance elastic bands will be supplied to all participants who are also given a booklet with detailed description and pictures of the exercises, as well as a form on which they can record their completion everyday. Only those who have completed 80% of the target can be considered eligible and enrolled in the final statistics. Finally, all follow-up assessments will be assessed by a blinded physiotherapist.

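### Eighty patients less 20% dropout leaves 32 per group, one short of the stated 33; a small slip in the inflation that should be restated

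*Protocol article*

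**What the plan says.** All the planning figures are in the Sample size section of the protocol article.

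- Difference to detect: "a change in VAS of knee pain is estimated to be 2.0 between two groups after the strengthening program".
- Variability: "the standard deviation (SD) between the experiment and the control groups is estimated to be 2.5".
- Error rates: "a two-tailed test with the power of 90% and the significance level of 5% (α error) is applied".
- Requirement before dropout: "the sample size required for each group is about 33".
- Final size: "Eventually, the total sample size is calculated to be 80 after taking into consideration a 1:1 allocation ratio and a dropout rate of 20" per cent.

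The Abstract and the Study population and allocation section repeat the total of 80, so 40 patients per group are planned. The section does not print the formula that takes 33 to 40.

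Two other sections decide who is analysed. Interventions says: "Only those who have completed 80% of the target can be considered eligible and enrolled in the final statistics". Statistical analysis plans both a per-protocol and an intention-to-treat analysis, the latter with last observation carried forward, and does not say which is primary.

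**The concern.** A dropout allowance should ensure that, once the assumed fraction is lost, the required number remains. That means dividing the requirement by the fraction retained. Multiplying by one plus the dropout rate always falls short, because the loss is taken from the larger, inflated number. The total of 80 looks like the product of that multiplication.

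At stake is whether the section's three statements (33 needed per group, 20% dropout, 80 in total) can hold together with 90% power. If they cannot, the trial report will carry a power statement that its own inputs do not support.

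**Working it through.** **Inputs** (all from Sample size): difference δ = 2.0, SD σ = 2.5, two-sided α = 0.05, power 90%, dropout d = 20%, allocation 1:1, total 80.

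**Step 1: reproduce the 33.** By the normal approximation for two means,

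n = 2 (1.960 + 1.2816)² σ² / δ² = 2 × 10.508 × 6.25 / 4 = 32.84, rounded up to 33 per group.

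This matches the protocol. By the t-test, 33 per group gives 89.3% power and 34 gives 90.2%, so 34 would be needed. The protocol's 33 is therefore the normal-approximation figure.

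**Step 2: look for the route to 80.**

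| Route | Per group | Total |
|---|---|---|
| 33 × (1 + 0.20) = 39.6 | 40 | 80 |
| 66 × (1 + 0.20) = 79.2 | 40 | 80 |
| 33 / (1 − 0.20) = 41.25 | 42 | 84 |
| 66 / (1 − 0.20) = 82.5 | – | 83 (84 for equal groups) |

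Only the multiplications give 80.

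**Step 3: apply the stated loss to the stated total.** 40 × (1 − 0.20) = 32 per group. This is below 33 and below the unrounded 32.84. The step does not depend on which formula was used.

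**Step 4: power at the sizes that matter.** By the normal approximation, power = Φ(δ / (σ√(2/n)) − 1.960). At n = 32: σ√(2/32) = 0.625, 2.0/0.625 = 3.20, 3.20 − 1.96 = 1.24, and Φ(1.24) = 0.893. The t-test values use the noncentral t distribution with 2n − 2 degrees of freedom.

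| n per group | Normal approximation | t-test |
|---|---|---|
| 32 | 89.3% | 88.3% |
| 33 | 90.1% | 89.3% |
| 34 | 91.0% | 90.2% |
| 40 | 94.7% | 94.2% |

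Going from 33 to 32 costs about one percentage point by either method.

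**Step 5: dropout that 80 patients can absorb at 90% power.** Normal approximation: 1 − 33/40 = 17.5%. t-test: 1 − 34/40 = 15%.

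**The case against.** The best reply is that almost nothing turns on this. The protocol says only about 33, the shortfall is one completer per group, and by the protocol's own method power falls to 89.3%, less than one point under target. That stands, and it settles the size of the point. It does not make the figures agree, because 32 is short even of the unrounded 32.84.

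A second reply is that the completer count may not be the relevant one. The intention-to-treat analysis with last observation carried forward keeps all 40 per group, and pain is scored weekly, so many early leavers would have a value to carry. Nominal power would then be 94.7% (94.2% by t-test), although only if carried-forward values were as informative as observed ones. This also stands: the shortfall applies to an analysis of completers. The point survives because a dropout allowance was made at all, which shows that the 33 were meant as patients with data.

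A third reply is that the multiplication is only inferred. That is true, but Step 3 does not need it.

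Three stronger readings are tempting, and the documents do not support them.

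- **The trial is materially underpowered.** One point of power does not show that. Setting the t-test's 88.3% against the target of 90% overstates the effect, because 33 per group already gives only 89.3% by that test.
- **The 80% completion rule in Interventions lowers power much further.** The article gives no non-adherence rate, does not say whether its 20% already includes patients who miss the target, and does not say that the restricted set is primary. Any power figure for this would be invented. All that can be said is that Sample size names no separate allowance for such exclusions.
- **Baseline adjustment will recover the shortfall.** The article gives no correlation between baseline and week 6, makes covariance adjustment conditional, and does not say whether the SD of 2.5 is for a change or a final score. The gain is unknown.

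**Conclusion.** The point holds as a minor arithmetic inconsistency. With 80 randomised and 20% lost, 32 per group remain, not the 33 that the section requires. An allowance that preserves 33 needs 42 per group, 84 in total, so the stated total is four short. Power among completers is 89.3% by the normal approximation or 88.3% by t-test.

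This rests on the protocol's own difference, SD, error rates and dropout rate, on equal losses in the two groups, and on an analysis limited to patients who do not drop out. It does not carry over to the intention-to-treat analysis, and it casts no doubt on the design.

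**What to change.** Keep 80 and correct the closing statement of Sample size, using one method throughout. Either of these would do:

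- *Normal approximation:* With 80 randomised and 20% dropout, 32 per group remain and power is about 89%; 90% power is kept for dropout up to 17.5%.
- *t-test:* With 80 randomised and 20% dropout, 32 per group remain and power is about 88%; 90% power is kept for dropout up to 15%. The requirement before dropout should then read 34 per group.

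The pairs should not be crossed: at 17.5% dropout, t-test power is 89.3%, not 90%.

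The sentence should also say that it refers to completers, and that no separate allowance is made for patients removed by the 80% completion rule in Interventions, if that is the case.

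The cost is a sentence or two of text and no extra patients. Raising the total to 84 would also restore consistency under the normal approximation, at the price of four more patients, but the size of the effect does not require it.

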### Statistical analysis

Statistical analyses will be performed following the per-protocol (PP) analysis and intention-to-treat (ITT) analysis. Typically, PP analysis would be conducted if no participants have dropped out of the trial for any reason. In addition, the rule of last-observation-carried-forward will be applied for the missing data when performing ITT analysis. Additionally, baseline data will be analyzed and adjusted using the covariance analysis if no statistically significant differences between two groups and a possibility of covariance of baseline data are found. Categorical data, such as gender or those expressed as frequencies (%) will be analyzed using chi-square test or Fisher’s exact test. Non-parametric statistical tests will be applied for data not conforming to normal distribution. In addition, statistically significant differences in intra-group and intergroup data will be analyzed by repeated measure analysis of variance. All statistical analyses will be performed using the SPSS 19.0 statistical software by a statistician blinded to the allocation. The significance level is set at 5%.

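### The protocol's rules for who is analysed conflict: ITT and PP are both promised, PP is tied to zero dropout, and an 80% completion rule governs the final analysis

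*Protocol article*

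**What the plan says.** Three statements in the protocol article bear on who is analysed.

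- Statistical analysis, opening sentence: "Statistical analyses will be performed following the per-protocol (PP) analysis and intention-to-treat (ITT) analysis". Both analyses are promised without condition.
- Statistical analysis, next sentences: "PP analysis would be conducted if no participants have dropped out of the trial for any reason", and for ITT "the rule of last-observation-carried-forward will be applied for the missing data when performing ITT analysis".
- Interventions, at the end of the description of home training: "Only those who have completed 80% of the target can be considered eligible and enrolled in the final statistics".

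The Sample size section shows that dropout is expected. It states that "the sample size required for each group is about 33" and that "the total sample size is calculated to be 80" after an allowance of 20% for dropout. The Outcomes section makes VAS pain at week 6 primary. No section says whether ITT or PP decides the comparison on that outcome.

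**The concern.** A PP analysis shows whether the conclusion survives when dropouts and protocol deviators are removed. Making it conditional on there being no dropouts withholds it when dropout could separate it from ITT. It also cancels the promise made one sentence before.

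The Interventions rule is the greater problem. Read plainly, it makes adherent participants the population of the final analysis, and that is not ITT. Adherence arises after randomisation, so selecting on it gives up the protection of random allocation. The arms also carry different exercise loads, so the fraction removed, and the kind of patient removed, may differ between them. A difference in week-6 pain among adherers could then partly reflect who managed to keep up.

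If the sets disagree, the protocol as written gives no rule for which result counts, and each can be defended from a different sentence.

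**Working it through.** **1. The plan's own sample size.** Inputs from the Sample size section: difference 2.0, SD 2.5, two-sided 5%, power 90%.

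n per arm = 2 × (1.960 + 1.282)² × (2.5/2.0)² ≈ 32.8, rounded up to 33. This matches. The total is 66 × (1 + 0.20) = 79.2, rounded up to 80, which also matches. (Dividing instead, 66/0.80, gives 83. That is a separate matter and plays no part here.)

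**2. How often the PP condition would be met.** With dropout probability d and independent dropouts, P(no dropout among 80) = (1 − d)^80. Only the 20% comes from the protocol; the other rates are assumed, to show the range.

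| d | Expected dropouts (80 × d) | P(no dropout) |
|---|---|---|
| 20% (planned) | 16 | 1.8 × 10⁻⁸ |
| 10% | 8 | 2.2 × 10⁻⁴ |
| 5% | 4 | 0.017 |
| 2% | 1.6 | 0.20 |
| 1% | 0.8 | 0.45 |

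**3. The sections side by side.**

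| Participant | ITT with LOCF (Statistical analysis) | 80% rule (Interventions) |
|---|---|---|
| Stays to week 12, does under 80% | in | out |
| Leaves early, under 80% done | in, last value carried forward | out |
| Does at least 80%, week-6 VAS missing | in, last value carried forward | in |

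The first two rows are direct contradictions. If the target is the full six-week programme, anyone who stops before 0.8 × 6 = 4.8 weeks cannot reach it. The 80% rule would then exclude many of the people for whom the carry-forward rule was written.

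**4. Why exclusion could differ by arm.** Each exercise is set at 10 repeats × 3 sets × 2 sessions = 60 repeats a day. Counting each exercise once, four exercises make 240 a day and two make 120. Reaching 80% means 192 a day in the experiment group and 96 in the control group. The protocol gives no adherence figures, so the resulting bias cannot be computed.

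**5. Power in a reduced set.** At 20% dropout, 64 participants (32 per arm) complete. Power is then about 0.89 by the normal approximation (0.88 by the t-test). If, as an assumption, one in five completers also missed the 80% target, 32 × 0.8 = 25.6, about 26 per arm, would remain, with power about 0.82 (0.81). The dropout allowance makes no mention of exclusions for low adherence.

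**The case against.** The strongest reply is that the PP sentence is a language slip. It may be meant to say that PP covers participants who did not drop out, and the article's English is loose elsewhere. That is plausible, and probably right. It means 0.8^80 measures how unworkable the printed condition is, not any bias, error rate or loss of power. A reader might infer that no PP analysis will ever be run. The document does not support that, because its opening sentence commits to PP without condition. What stands is that the two sentences conflict as printed.

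A reader might also infer that the headline set switches with the observed dropout: PP if nobody leaves, ITT otherwise. The text allows that reading but does not state it. At the planned dropout such a switch would almost always select ITT, so it would do little harm.

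Nor is it right that PP adds nothing when nobody drops out. A participant can attend every visit and still do under 80% of the home exercise, so the two sets can differ through adherence alone.

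Finally, the ranking of analysis sets may be left to a statistical analysis plan that is not shown. Silence on ranking alone would not be a finding. But the protocol is not merely silent: it fixes an 80% rule for the final analysis alongside ITT, and a later plan would have to override one of them.

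**Conclusion.** The point holds as a contradiction between the Interventions and Statistical analysis sections, together with a PP condition that conflicts with the sentence before it. At the planned 20% dropout, that condition has a probability of about 2 × 10⁻⁸ of being met. This assumes independent dropouts and takes the planning allowance as the true rate; at an assumed 5% it is still only 1.7%.

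The consequential part is the 80% completion rule, which excludes participants on post-randomisation adherence and cannot coexist with ITT as the final analysis. Whether it would bias the week-6 VAS comparison, and in which direction, depends on adherence by arm, which the document does not give. A reader might infer that ITT has been abandoned. It has not: it is promised, with a missing-data rule. What is missing is a statement that it prevails.

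**What to change.** Three changes to the text, made together:

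1. In Statistical analysis, state that ITT of all randomised participants is the primary analysis and alone decides superiority on week-6 VAS pain.
2. Delete the no-dropout condition. State that PP will be run in all cases, whatever the number of dropouts, and reported as supportive.
3. In Interventions, confine the 80% completion rule to the definition of the PP set, so that it no longer governs entry to the final analysis. If this sentence is left as it is, it will contradict the first change.

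The cost is wording and one additional run of the same model. The sample size does not change.

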**Methods:**

A total of 80 subjects with symptomatic KOA will be recruited from the communities and hospital outpatient, and will be randomly assigned to the experiment group (Quadriceps-plus-hip-abductor-strengthening) or the control group (Quadriceps-strengthening). Specifically, participants in the experiment group will complete 4 exercises to train the quadriceps and hip abductor twice a day for 6 weeks at home, while those in the control group will only perform 2 exercises to strengthen the quadriceps. Besides, all patients will also receive usual care management, including health education and physical agent therapy when necessary. Knee pain will be measured using the Visual Analogue Scale (VAS) at baseline, in every week during the course of treatment, as well as 8 and 12 weeks after randomization. Furthermore, knee function will be measured using the Western Ontario and McMaster Universities Osteoarthritis Index (WOMAC) scale, and the quality of life will be measured using the MOS Item Short-form Health Survey (SF-36). In this study, several simple tests will be applied to assess the objective function. All the assessments except for VAS will be carried out at baseline, and in the 6th, 8th and 12th weeks respectively.

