### Outcomes

Participants will be assessed by other physiotherapists blinded to the group allocation at different time points based on different assessments shown in Table 1. Additionally, baseline age, gender, symptoms, disease severity (K-L grade), duration, previous treatment and medication will be recorded using a questionnaire (in week 0). The primary outcome is the overall pain assessed using VAS in the 6th week, while the secondary outcomes include the overall function measured by the Western Ontario and McMaster Universities Osteoarthritis Index (WOMAC), as well as the quality of life assessed by MOS Item Short-form Health Survey (SF-36), and several functional tests.

**Table 1 Tab1:** Schedules for follow-up assessments and date collection

Assessments	Baseline	Active strengthening at home						Follow-up	
	Week 0	1st week	2nd week	3rd week	4th week	5th week	6th week	8th week	12th week
VAS for pain	√	√	√	√	√	√	√	√	√
WOMAC	√						√	√	√
SF-36	√						√	√	√
FTSST	√						√	√	√
Step test	√						√	√	√
Stair ascent/descent task	√						√	√	√
Figure-of-8 Walk Test	√						√	√	√
Adverse effects		√	√	√	√	√	√	√	√

The overall pain intensity in the involved knee within the past 1 week will be self-measured by patients using the VAS, with terminal descriptors ranging from 0 (no pain) to 10 (maximal pain). Meanwhile, the overall function of patients will be assessed adopting WOMAC, a disease-specific scale with high reliability and validity [23]. WOMAC is comprised of 24 items assessing pain (scored 0–20), stiffness (scored 0–8) and physical functions (including personal care, walking, sitting, lifting, sleeping, standing, social life and travelling) (scored 0–68). Every item is rated on a scale of 0–5, with a higher score indicating a worse symptom. Moreover, the quality of life will be measured by SF-36 constituted by eight dimensions, including mobility, pain and discomfort, daily activities, depression and anxiety, and self-care [24].

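### LOCF as the only missing-data rule can distort the week-6 pain comparison in either direction, and for the other outcomes it carries baseline forward

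*Protocol article*

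**What the plan says.** On missing data, the Statistical analysis section of the protocol says that "the rule of last-observation-carried-forward will be applied for the missing data when performing ITT analysis". It names no other rule and no sensitivity analysis. The analysis across groups and over time is a repeated-measures analysis of variance.

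The Outcomes section fixes the endpoint: "The primary outcome is the overall pain assessed using VAS in the 6th week". The Abstract (Methods) and Table 1 schedule VAS at baseline, then "in every week during the course of treatment, as well as 8 and 12 weeks after randomization". Table 1 schedules WOMAC, SF-36 and the four functional tests only at baseline and weeks 6, 8 and 12.

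Under Interventions, both arms see a physiotherapist "once a week for 6 weeks, so as to learn the exercises and adjust the training intensity", and resistance can be progressed. The experiment arm does four exercises and the control arm two. The Sample size section assumes that "a change in VAS of knee pain is estimated to be 2.0 between two groups after the strengthening program", with an SD that "is estimated to be 2.5 based on relevant previous publications", and allows for 20% dropout.

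**The concern.** LOCF takes pain to stay where it was at the last visit attended. This trial is planned on the opposite expectation: pain should change over a six-week programme whose load is reviewed weekly, and the arms should differ by 2.0 points afterwards. A patient last seen at week 2 is entered at week 6 with the week-2 value, and again at weeks 8 and 12.

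How far this moves the comparison depends on how many patients leave each arm and when. The arms differ in burden, so unequal dropout is plausible, although the protocol does not predict it. At stake is the estimated week-6 difference, with one patient in five expected to drop out. The rule is also avoidable, because the weekly VAS values already collected support a better analysis.

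**Working it through.** **The plan's own figure.** n per arm = 2 × [2.5 × (1.960 + 1.282) / 2.0]² = 32.8, so 33, as stated. The total of 80 follows as 33 × 1.2 ≈ 40 per arm. The inputs δ = 2.0, SD = 2.5 and 20% dropout are those of the Sample size section.

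**Assumptions not in the protocol.** VAS falls linearly to week 6. The control arm falls by c = 1 or 2 points and the experiment arm by c + δ. Dropout is unrelated to outcome. Split of dropout by arm and its timing are varied.

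**Share of the fall that LOCF loses.** A dropout last seen at week w (0 to 5) loses (6 − w)/6 of the fall. If leaving is spread evenly, the mean loss is m = (6 + 5 + 4 + 3 + 2 + 1)/36 = 21/36 = 0.583.

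**Expected LOCF estimate at week 6**, with dropout d before week 6 and mean loss m in each arm (E experiment, C control):

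(c + δ)(1 − d_E m_E) − c(1 − d_C m_C)

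Example with 30% versus 10% and c = 2: 4 × (1 − 0.175) − 2 × (1 − 0.0583) = 3.30 − 1.883 = 1.42.

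| Dropout before week 6 (E / C) | Timing | δ = 2.0: c = 1 | δ = 2.0: c = 2 | δ = 0: c = 1 | δ = 0: c = 2 |
|---|---|---|---|---|---|
| 20% / 20% | even | 1.77 | 1.77 | 0 | 0 |
| 10% / 10% (half of the 20% leaves later) | even | 1.88 | 1.88 | 0 | 0 |
| 25% / 15% | even | 1.65 | 1.59 | −0.06 | −0.12 |
| 30% / 10% | even | 1.53 | 1.42 | −0.12 | −0.23 |
| 10% / 30% | even | 2.00 | 2.12 | +0.12 | +0.23 |
| 20% / 20% | E early (m = 5/6), C late (m = 1/6) | 1.53 | 1.40 | −0.13 | −0.27 |
| 20% / 20% | E late, C early | 2.07 | 2.20 | +0.13 | +0.27 |

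The table varies either rate or timing. If both differ in the same sense, the range widens to 1.03 to 2.43, and to ±0.47 under no effect (c = 2). That stacks two undocumented assumptions, and the point does not rely on it.

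**Simulation check** (2,000 trials per pattern, 40 per arm, week-6 SD about 2.5). LOCF averaged 1.76 at 20%/20%, 1.42 at 30%/10% (c = 2) and 2.12 at 10%/30% (c = 2). The simulated late leavers left at week 4 on average, a milder pattern than in the table, so the timing cases (c = 2) came out at 1.48 and 2.08. A likelihood-type sequential regression on the same weekly values averaged 1.98 to 2.03 when the truth was 2.0, and −0.04 to 0.01 when it was 0.

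**Secondary outcomes.** With no visit between baseline and week 6, anyone leaving before week 6 loses the whole change, so m = 1. With 20% leaving each arm before week 6, the estimate is (c + δ) × 0.8 − c × 0.8 = 0.8δ, or 80% of the true effect.

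**The case against.** **The illustration rests on undocumented inputs.** No weekly pain course is given. If most of the fall comes early, carried values lie closer to week 6 and the bias shrinks. Entry pain must lie between 2 and 7, so the 4-point experiment-arm fall implied by c = 2 is large. A 30% versus 10% split has no support in the protocol. The 20% is not timed, and losses after week 6 do not touch the primary endpoint. All of this stands, which is why the table includes c = 1, 25%/15% and half the dropout after week 6. It reduces the size but does not make LOCF fit an outcome that is expected to change.

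**A reader might infer that the week-6 estimate is certainly biased.** The protocol does not support that. With no true effect and equal dropout and timing the bias is zero, and some unequal patterns cancel (10%/30% with c = 1 gives 2.00). Nor does the protocol say whether the ITT or the per-protocol analysis is primary. The Interventions section also limits the final statistics to patients who completed 80% of the target. How much weight the LOCF-filled analysis carries is therefore itself unsettled.

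**A reader might also infer that the standard error is too small because filled-in values are treated as observed.** For the week-6 comparison between arms this does not hold: each patient supplies one value and patients are independent. In 20,000 simulated trials, actual and mean estimated standard errors were 0.546 and 0.542 (no effect, 20%/20%), 0.539 and 0.541 (no effect, 30%/10%), and 0.564 and 0.562 (effect 2.0, 20%/20%). Rejection under no effect was 5.1% at 20%/20% and 7.3% at 30%/10%, the excess coming from the shifted mean.

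**Conclusion.** The point holds as a risk of bias in either direction. The protocol fixes LOCF as its only missing-data rule for ITT, on an endpoint where change up to week 6 is the premise of the trial.

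Under the linear-fall assumptions, a true 2.0 is estimated as about 1.77 with 20% dropout per arm before week 6, or 1.88 if half of the dropout comes later. The estimate is about 1.4 to 1.65 when the experiment arm loses more patients (25–30% versus 10–15%), and up to about 2.2 when controls leave more often or earlier. With no true effect the bias is 0 for equal dropout and timing, and up to about 0.27 points either way when rates or timing differ. Because overestimates occur, LOCF cannot be defended as conservative. Secondary outcomes lose more per early dropout, since baseline itself is carried forward.

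These are illustrations, not predictions: they need a steady fall in pain and dropout unrelated to outcome. The design survives, but the analysis wording should change before the data are analysed.

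**What to change.** Replace LOCF for VAS by a likelihood-based mixed model for repeated measures on all observed post-baseline values. Include group, visit, group-by-visit and baseline VAS, with the week-6 contrast as primary. Eight post-baseline visits with an unstructured covariance need 8 × 9 / 2 = 36 parameters from 80 patients. Prespecify a simpler covariance in case the model does not converge, or restrict it to weeks 1–6 (6 × 7 / 2 = 21 parameters).

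Use the same type of model for the secondary outcomes at weeks 6, 8 and 12. Add a delta-adjusted sensitivity analysis, and keep LOCF at most as a further sensitivity analysis.

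The cost is revised wording and modest programming, with no new visits, data or patients. The plan names SPSS 19.0, so confirm that the delta-adjusted analysis can be run there or name another tool. The main drawback is reliance on missing-at-random, which the simulation satisfied by construction and the delta-adjusted analysis is there to probe.

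### Covariance adjustment depends on a baseline significance test and, as worded, is provided only when the arms do not differ; it should be unconditional

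*Protocol article*

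**What the plan says.** Under Outcomes, the article states: "The primary outcome is the overall pain assessed using VAS in the 6th week". Table 1 schedules VAS at week 0 as well, so a baseline value is planned for every participant.

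Under Statistical analysis, baseline data are to be "adjusted using the covariance analysis if no statistically significant differences between two groups and a possibility of covariance of baseline data are found". Two conditions must therefore hold before covariance adjustment is used: the baseline test is non-significant, and baseline data are judged possibly to covary. The second condition is not defined. Nothing in the article provides for adjustment when the first condition fails.

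For the group comparison the same section says that "statistically significant differences in intra-group and intergroup data will be analyzed by repeated measure analysis of variance". It names no baseline covariate there and does not say whether week 0 is one of the time levels. A 5% significance level is set for the analyses; no separate level is given for the baseline test.

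**The concern.** Two faults sit in one sentence.

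- **Conditionality.** Allocation is randomised, so any baseline difference between the arms is a chance one. A test of it examines a null hypothesis already known to be true and is no sound basis for choosing a model. The choice also leaves the primary model open until data have been seen, and the undefined second condition adds discretion.
- **Direction.** As worded, adjustment is available when the arms look alike and is not provided when they differ. That is the case in which an unadjusted estimate is pulled furthest by the imbalance.

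At stake are the week-6 VAS estimate in a trial that happens to be imbalanced, and the credibility of an adjustment decided after looking at the data.

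**Working it through.** **The plan's own figure.** Sample size gives a difference ("a change in VAS of knee pain is estimated to be 2.0 between two groups after the strengthening program") and an SD ("the standard deviation (SD) between the experiment and the control groups is estimated to be 2.5"), with two-sided 5% and 90% power. Then n per group = 2 × (1.960 + 1.282)² × (2.5/2.0)² = 2 × 10.51 × 1.5625 ≈ 32.8, so 33, as stated. The total of 80 follows from 66 × 1.2 = 79.2. With 40 per arm and 20% dropout, 40 × 0.8 = 32 per arm remain, and 32 is used below.

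**Assumptions not in the article.** The baseline to week-6 VAS correlation r is 0.3, 0.5 or 0.6. Scores are normal with SD 2.5 at both times. The baseline test is a two-sided t-test at 5%. The second condition is always met.

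**Strategies compared by simulation.** Always ANCOVA; the rule as written (ANCOVA only if baseline p ≥ 0.05, otherwise an unadjusted week-6 comparison); and the reverse rule (ANCOVA only if baseline p < 0.05).

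**Trials with a significant baseline difference.** About 5% of randomised trials have one, with a mean size of about 0.57 SD. The expected shift of an unadjusted week-6 difference is r × 2.5 × 0.57:
- r = 0.3: 0.43 points
- r = 0.5: 0.71 points
- r = 0.6: 0.86 points

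A change-from-baseline contrast is shifted by (r − 1) × 2.5 × 0.57 = −1.00, −0.71 and −0.57 points, that is, away from the imbalance.

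| With no treatment effect | r = 0.3 | r = 0.5 | r = 0.6 |
|---|---|---|---|
| False rejection in imbalanced trials, unadjusted week 6 | 9% | 17% | 26% |
| False rejection in imbalanced trials, change from baseline | 24% | 18% | 14% |
| False rejection in imbalanced trials, ANCOVA | about 5% | about 5% | about 5% |
| Overall type I error, rule as written | 5.1% | 5.6% | 6.1% |
| Overall type I error, reverse rule | 4.7% | 4.3% | 3.9% |

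The overall figure for the written rule can be checked by hand. At r = 0.5, 0.05 × 17% + 0.95 × 5% = 0.85% + 4.75% = 5.6%. Runs with 33 per arm gave conditional rates of 9.7% and 18.3% at r = 0.3 and 0.5, so these rates are good to about one percentage point.

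**Power for a difference of 2.0, 32 per arm.**

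| | r = 0.3 | r = 0.5 | r = 0.6 |
|---|---|---|---|
| Rule as written | 90.4% | 94.1% | 96.1% |
| Always ANCOVA | 90.6% | 94.9% | 97.4% |
| Gain (percentage points) | 0.2 | 0.8 | 1.3 |

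Against the reverse rule, which leaves about 95% of trials unadjusted, always adjusting gains about 2 to 8 percentage points.

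**The case against.** The strongest reply is that the sentence is awkward English and the 'no' is unintended. Non-adjustment under imbalance is only implied by the 'if', and the sentence speaks of baseline data in general without naming VAS. This has force: if the opposite was meant, the false-rejection figures for imbalanced trials no longer apply. The dependence on a baseline test remains, however. The test would then be slightly conservative, and the loss of power would be larger than under the literal reading.

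A second reply is that such detail belongs in an analysis plan. That does not answer the point, because the article states a rule and the rule is faulty.

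A reader might also infer more than the article supports:

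- **That adjustment would lift power from 88% to 91–98%.** The 88% belongs to never adjusting. The written rule, with its second condition met, adjusts in about 95% of trials, so the gain over it is much smaller.
- **That 10–26% is the trial's false-positive rate.** Those rates apply only within about 1 trial in 20.
- **That the estimate is wrong by 0.6 to 0.9 points because of the rule.** That is the mean absolute error of the unadjusted estimate in imbalanced trials, and it includes ordinary sampling noise. The standard error is 2.5 × √(2/32) = 0.625, and 0.80 × 0.625 = 0.50 points arises from noise alone. ANCOVA in the same trials still gives about 0.4 to 0.5. The shift is the cleaner measure.
- **That the plan prescribes an unadjusted week-6 test under imbalance.** It names no fallback other than repeated-measures ANOVA. If week 0 is a time level, the relevant contrast behaves like change from baseline, and the pattern across correlations reverses.

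**Conclusion.** The point holds with limited size. The stated rule makes the model depend on a baseline test and, read literally, provides adjustment only when it is least needed. Averaged over all trials the damage is modest: type I error of about 5.1% to 6.1% as written, or about 4.7% to 3.9% if the rule was meant the other way round. It is serious only if this trial turns out to be imbalanced. Then either unadjusted reading rejects falsely well above 5%, with shifts of about 0.4 to 1.0 points in one direction or the other, set against a target of 2.0.

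All of these figures rest on the assumed correlations. The change-from-baseline figures also assume equal SDs at both times. Eligibility limits average pain to between 2.0 and 7.0, which may make the baseline SD smaller, so those figures are indicative only. The sentence should be corrected, but it does not by itself invalidate the design or the sample size.

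**What to change.** Replace the sentence with: *Week-6 VAS will be compared between groups with baseline VAS as a covariate in all cases, irrespective of any baseline difference.* Treat each secondary outcome that has a baseline measurement the same way, using its own baseline. Do not use baseline significance tests to choose the model. The section should also say how this comparison relates to the repeated-measures ANOVA.

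The cost is a sentence or two of text. Baseline values are already scheduled in Table 1, and the sample size can stay as it is. The change should be made before any unblinded analysis, because an adjustment chosen afterwards would not be credible.
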